### Assignment of interventions: blinding

#### Who will be blinded {17a}

The trained junior researchers, the responsible clinical staff, and the patients themselves will be blinded to avoid any potential influence, whether conscious or unconscious.

#### Procedure for unblinding if needed {17b}

N/a (since our intervention will be supplementary and will not modify the process or medications, identification of blinding is unnecessary).

### Data collection and management

#### Plans for assessment and collection of outcomes {18a}

##### Baseline

Patients will be pseudonymized after inclusion. Required data items encompass Montral Cognitive Assessment (MOCA) [25], Frailty-test [26], PONV risk score [23], and continuous medication including pain medication. Additionally, patients will complete the Quality-of-Life questionnaire (SF-36) [27], Geriatric Depression Scale (GDS) [28], and instrumental Activities of Daily Living (iADL) [29].

##### Before surgery

Directly prior to their scheduled surgery patients will be visited for assessment. The patients’ cognitive state will be assessed using the 4AT. Additionally, they will be asked to rate their current level of pain using the NRS, as well as provide a saliva sample for cortisol analysis. Blood samples for cortisol levels and biomarkers will be obtained within the placement of a peripheral venous access, without the need for a separate puncture.

##### Throughout surgery

The following data will be recorded routinely. During anaesthesia depth of anaesthesia will be monitored intraoperative processed EEG, employing devices such as Sedline® [30]. Other crucial parameters are analgesic use, NOL-index [12] evaluated pain levels, overall operating time, and recovery duration, measured from the end of sedation to the time of extubating.

##### After surgery

After extubating objective data will be collected in the recovery room every 15 min for a total duration of 1 h. Postoperative assessments will include the 4AT score for delirium, pain score measured on NRS, Numerical Comfort Scale (NCS) for assessing comfort, and postoperative nausea rated from 0 to 3. After the patient will have been in the recovery room for 1 h, additional assessments will be conducted, including an extended delirium screening (3DCAM), PONV Score antiemetic consumption, and nurse-controlled analgesia consumption for NRS 3.

In the regular ward, data will be recorded for the first 5 days post-surgery: pain scores (measured using the NRS); analgesic intake via nurse-controlled analgesia (NCA; applicable for NRS of 3 or higher); PONV scores (as per Wengritzky’s classification system); antiemetic usage, comfort ratings (using the NCS); and delirium assessments (using both the 4AT score and 3DCAM) will be documented.

Follow-up assessments will be conducted 3 months after the surgery by sending patients a set of questionnaires (iADL, GDS, BDI, SF36) via mail. They will also be asked to provide their pain and comfort levels (NAS and NCS, respectively) and to submit another saliva sample. Any adverse effects that may have occurred will also be investigated and noted. If any cause for concern arises about returned questionnaires, the participants will be contacted and offered further assistance. All study participants may contact us at any time should they have any questions or concerns.

#### Plans to promote participant retention and complete follow-up {18b}

To enhance participant retention, trained junior investigators will supervise participants during their clinical stay. Study results as well as personal blood work results will be provided to patients at the study’s conclusion if they have agreed to receive them.

A 3-month follow-up will yield additional information on participants’ well-being, and, when needed, further supportive discussions will be arranged.

If participants choose to withdraw from the study, all data collected from them will be eliminated and excluded from the analysis. Withdrawal will be permitted at any point.

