**Methods:**

This randomized controlled double-blinded trial will involve patients aged 60 and above undergoing elective hip or knee surgery under general anesthesia. Participants will be randomized into three groups: a control group receiving no auditory intervention and two intervention groups receiving positive therapeutic suggestions via headphones from either a male or female speaker. The primary outcome is the incidence of postoperative delirium within 5 days after surgery that will be assessed by using the 4AT and 3DCAM. Secondary outcomes include pain intensity, which is measured intraoperative by nociception level index (NOL) and postoperative by NRS, medication consumption as well as postoperative nausea and vomiting. Data will be collected before, during, and after surgery as well as 3 months after surgery.

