### Criteria for discontinuing or modifying allocated interventions {11b}

Consent to participate in the study can be withdrawn at any time, without giving reasons or obtaining any disadvantages for further medical care. In case of withdrawal from the study, personal data already obtained will be destroyed. Patients for whom there will be a short-term change in the anaesthetic procedure, e.g., to anaesthesia with sevoflurane, will be considered separately due to the increased risk of PONV.

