ALLOCATION														
Randomized allocation		●												
SAMPLES														
Blood sample			●											
Saliva sample			●											●
INTERVENTION														
Controll group				●										
SGS intervention group				●										
DGS intervention group				●										
OUTCOME VARIABLES														
4AT Delirium			●		●	●	●	●	●	●	●	●	●	
3DCAM Delirium								●	●	●	●	●	●	
Pain score (NAS)			●		●	●	●	●	●	●	●	●	●	●
Pain medication consumption			●					●	●	●	●	●	●	●
Comfort scale (NCS)			●		●	●	●	●	●	●	●	●	●	●
PONV wengritzky								●	●	●	●	●	●	
Sedline				●										
NOL				●										

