#### Methods in analysis to handle protocol non-adherence and any statistical methods to handle missing data {20c}

In general, per-protocol analysis will be intended. To address the fact that complete protocol adherence is not always feasible in everyday clinical practice, all relevant cases will be included in the calculations as part of an intention-to-treat analysis.

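### Erasing all data of randomised patients who withdraw, including recorded delirium outcomes, does not fit the intention-to-treat analysis in {20c}

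*Protocol article*

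**What the plan says.** Two sections of the protocol article set the rule for patients who withdraw. Section {18b} (retention and follow-up) states that "all data collected from them will be eliminated and excluded from the analysis", and adds: "Withdrawal will be permitted at any point". Section {11b} (discontinuing or modifying interventions) states: "In case of withdrawal from the study, personal data already obtained will be destroyed".

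The analysis population is described in {20c}. It opens with "In general, per-protocol analysis will be intended" and then says that, because full adherence is not always feasible, "all relevant cases will be included in the calculations as part of an intention-to-treat analysis".

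Two facts fix the timing. The participant timeline in {13} places "Randomized allocation" at the baseline visit, before surgery. The abstract defines the endpoint: "The primary outcome is the incidence of postoperative delirium within 5 days after surgery". In the same timeline, postoperative delirium assessments run from the recovery room to day 5.

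**The concern.** The period in which a patient can withdraw includes the whole period in which the primary outcome is recorded. A patient who is randomised, screens positive for delirium on day 1 and withdraws on day 3 leaves no trace in the analysis. An intention-to-treat analysis is meant to count such a patient in the allocated arm.

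The per-protocol sentence does not resolve this, because erasure removes the patient from either population. Nor can a later analysis plan: once the assessment is destroyed, it cannot be analysed or used to inform an imputation.

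The outcome makes this more than a formality. Delirium disturbs attention and awareness, and it is detected here by cognitive testing repeated over several days. It is plausible, though not documented, that affected or distressed patients would withdraw more readily. The loss would then depend on the outcome being measured.

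**Working it through.** **1. The passages side by side.**

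| Section | Rule |
|---|---|
| {13} | Randomised at baseline; delirium assessed to day 5 |
| {18b} | Withdrawal possible at any time; all data eliminated and excluded from analysis |
| {11b} | Data already obtained are destroyed on withdrawal |
| {20c} | Per-protocol generally intended; intention-to-treat on all relevant cases |

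The term "personal data" in {11b} might mean identifying data only. The wording of {18b}, which covers all data collected and excludes them from the analysis, leaves no room for that. The {18b} rule and the intention-to-treat sentence therefore cannot both hold for a randomised patient who withdraws.

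**2. The plan's own figure for loss.** Section {14} adds 10% to 248: 248 × 1.10 = 272.8, so 273, rounded up to 280. The stated figure is reproduced. Dividing instead gives 248 / 0.90 = 275.6, so 276. The target of 280 covers both, since 280 × 0.90 = 252. The allowance protects the number of patients, not against loss related to outcome.

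**3. Inputs for an illustration.** From {14}: 25% delirium in control, halved to 12.5% under intervention, and 280 patients, which is 140 per arm. Assumed, because the documents give none: withdrawal proportions w1 among delirious and w0 among non-delirious patients. Also assumed: a two-sided 5% test, as sidedness is not stated.

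Observed rate = p(1 − w1) / [p(1 − w1) + (1 − p)(1 − w0)]

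**4. Outcome-related withdrawal, equal in both arms (w1 = 25%, w0 = 5%).**

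- Control: 0.25 × 0.75 = 0.1875; 0.75 × 0.95 = 0.7125; 0.1875 / 0.9000 = 20.8%.
- Intervention: 0.125 × 0.75 = 0.09375; 0.875 × 0.95 = 0.83125; 0.09375 / 0.92500 = 10.1%.
- The difference is 10.7 points instead of 12.5.
- Patients left: 140 × 0.900 = 126 and 140 × 0.925 = 129.5.
- Power (normal approximation) is about 66%. It is 72% with a 10% loss unrelated to outcome (126 per arm), and 77% with all 140 per arm retained and their outcomes known.
- The odds ratio does not move: true (0.125/0.875) / (0.25/0.75) = 0.429; observed (0.09375/0.83125) / (0.1875/0.7125) = 0.429. The distortion is in incidence, absolute effect and power.

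**5. No true effect (25% in both arms).**

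| Assumed withdrawal | Observed, control vs intervention | Two-sided error |
|---|---|---|
| 10% unrelated to outcome, both arms | 25.0% vs 25.0% | 5% |
| 25% / 5% in both arms | 20.8% vs 20.8% | 5% |
| 25% / 5% in intervention only; 10% unrelated in control | 25.0% vs 20.8% | about 12% |

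Only the last row, where the pattern differs by arm, produces a false difference (4.2 points).

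**6. What bounds can still show.** Suppose the remaining patients show 25% vs 12.5% and a fraction w is erased in each arm. The lower bound takes every erased intervention patient and no erased control patient as delirious: 0.25(1 − w) − [0.125(1 − w) + w]. The upper bound reverses this: [0.25(1 − w) + w] − 0.125(1 − w).

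| w | Lower | Upper |
|---|---|---|
| 2% | 10.25 points | 14.25 points |
| 5% | 6.875 points | 16.875 points |
| 10% | 1.25 points | 21.25 points |

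These need only arm and count. Retained outcomes would narrow them; destroyed ones cannot.

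**The case against.** The strongest defence has four parts.

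- **Blinding.** Patients, clinical staff and assessors are blinded ({17a}). Control patients wear headphones with empty tracks, and the audio starts only after loss of consciousness. Nothing in the documents would drive withdrawal differently by arm. This stands. A reader might infer that the rule will manufacture a benefit; the documents do not support that. One can construct a case: 35/140 vs 25/140 gives p = 0.145, and erasing four delirious intervention patients (21/136) gives p = 0.048. But the counts are invented, and every erasure is a delirious patient in one arm. The result also holds only for the uncorrected chi-square (0.068 with continuity correction, 0.053 by Fisher's exact test). Erasing four delirious patients from each arm gives 31/136 vs 21/136 and p = 0.123.
- **Withdrawal is narrower than non-response.** A reader might infer that declining the 3-month questionnaires, or refusing one cognitive test, triggers deletion. The text attaches deletion to withdrawal from the study, so a skipped assessment is ordinary missing data. Likewise, the 10% in {14} is for drop-outs in general and is not a forecast of erasures.
- **Sensitivity analysis remains possible.** It would be too strong to say that erasure rules it out. Bounds and tipping-point analyses need only arm and count, and an analysis without the withdrawn patients can still be run. What is lost is the recorded outcome.
- **The intention-to-treat promise is loose.** It covers relevant cases and sits behind a per-protocol intention. This makes the contradiction less sharp, but does not remove it: no usual meaning of intention-to-treat drops a randomised patient whose primary outcome was recorded.

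A patient's right to ask for erasure is not in dispute. The weakness is that deletion is automatic.

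**Conclusion.** The inconsistency is real. It lies in stated rules, not in a detail left to a fuller document. Sections {18b} and {11b} remove randomised patients together with recorded delirium outcomes, and {20c} announces an intention-to-treat analysis without reconciling the two.

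The effect on the result cannot be sized, because the documents give no withdrawal rates by outcome or arm. If delirious patients withdraw more often to the same degree in both arms, incidence and the absolute difference are understated and power falls. Under the assumed 25% and 5%, 12.5 points shrink to 10.7, and power is about 66% rather than 72%. If withdrawal is unrelated to outcome, only numbers are lost. A false difference needs outcome-related withdrawal that also differs by arm, which is possible but less likely under blinding. The change is worth making because the loss is irreversible and the remedy cheap.

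**What to change.** - **{11b} and {18b}:** distinguish stopping further assessments from withdrawing consent to the use of data. For patients consented from now on, keep the pseudonymised data collected up to withdrawal by default, analyse them as randomised, and erase only on explicit request.
- **{20c}:** state that intention-to-treat includes patients who withdraw after randomisation, using the data collected to that point, and say how this relates to the per-protocol analysis.
- **Patients already promised deletion:** honour the promise. Where permitted, keep only arm and count, report erasures by arm in the flow diagram, and add best/worst-case or tipping-point bounds for the primary outcome.

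The cost is an ethics amendment to the withdrawal and consent wording. It reaches only patients enrolled after it. Enrolment began in November 2022 and data collection was expected to run until October 2025, so these may be few. The counts by arm and the bounds cost little and remain useful for the whole trial.

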#### Data management {19}

The RedCap online tool (Vanderbilt University, Texas, USA) will serve as a shared database for all participating centers hosted by the Ruhr University Bochum. Patient data will exclusively be entered using pseudonyms, preventing any conclusions about the individuals without further information. During the study, data will be recorded on paper protocols or directly via RedCap. RedCap supports data quality assurance by enforcing specific data formatting and performing range checks during data entry. After completing data collection, we will conduct plausibility checks.

#### Confidentiality {27}

Patients’ confidential information will be protected under medical confidentiality and the German Federal Data Protection Act (BDSG). Pseudonymized proband data may be shared, but original documents will not be accessible to third parties.

#### Plans for collection, laboratory evaluation and storage of biological specimens for genetic or molecular analysis in this trial/future use {33}

On the day of surgery, a blood sample will be drawn to quantify relevant values and cryopreserve biomarkers. In addition, a saliva sample will be taken to analyze preoperative cortisol as a marker for experienced stress.

### Statistical methods

#### Statistical methods for primary and secondary outcomes {20a}

To ensure normal distribution, the Kolmogorov–Smirnov test will be conducted prior to further analyses. Statistical significance will be considered at a *p*-value < 0.05. The primary outcome (postoperative delirium incidence) and other binary outcomes (e.g., incidence of postoperative nausea and vomiting, PONV) will first be compared between the intervention and control groups using the chi^2^ test. Continuous non-parametric variables will be analyzed with Mann–Whitney *U* tests, and parametric variables with Student’s *t*-test. To account for potential confounding effects of intraoperative and postoperative medication use, detailed data on the type and dosage of analgesics and sedatives will be collected. These variables will be included as covariates in multivariable logistic regression models for binary outcomes (e.g., delirium, PONV) and multivariable linear regression models for continuous outcomes (e.g., postoperative pain scores, NRS; intraoperative NOL index values). Confounders will be selected a priori based on clinical relevance and evidence from previous literature to avoid data-driven overfitting.

Medication-related parameters (e.g., total opioid dose, intraoperative sedative use) will also be analysed descriptively and compared between groups. Sensitivity analyses will be performed to assess the robustness of the results with and without adjustment for these covariates.

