### Objectives {7}

In the current study, we aim to address the following hypotheses:

Primary hypothesis:Delirium incidence is lower in the intervention group than in the control group

Secondary hypotheses:2)Pain intensity is lower in the intervention group than in the control group3)Intraoperative: NOL values are lower in the intervention group than in the control group4)Postoperative: NRS values are lower in the intervention group than in the control.5)Pain medication consumption p.p. is lower in the intervention group than in the control group6)Postoperative nausea and vomiting (PONV) incidence is lower in the intervention group than in the control group

Exploratory analyzation:7)The above-mentioned effects differ depending on whether the subjects hear a speaker’s voice according to their own gender or not

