### Sample size {14}

Based on the primary endpoint analysis, the sample size was calculated as follows:

At the university hospital, LMU Munich, a delirium incidence of approx. 25% can be assumed for electively orthopedic surgery. By means of therapeutic suggestion may be reduced by at least 50%. The calculation in G*Power [24] using the z-test “Difference between two independent proportions” results in a sample size of 110 subjects per group for a design in which the intervention group and control group are of equal size, with a required power of at least 0.8 and a significance level of 5%. This results in a total of 220 subjects.

Based on the results of the study by Nowak et al. 2020 [11], we also calculated the sample size needed to detect effects of the intervention on pain expression, which are of great interest in the secondary endpoint analysis: For effects on opioid use, an effect size of *d* = 0.36 is assumed. For a required power of 0.8 at a level of significance at 5%, a group size of at least 101 subjects is needed. For effects on pain intensity, an effect size of 0.325 can be calculated using G*Power based on the mean values and standard deviations given in the original work. When power is set at 0.8 and significance level at 5%, the resulting sample size amounts to a total of 248 subjects.

In addition to the effect of the intervention on delirium incidence, the effect on pain severity is also of great interest as a (secondary) endpoint. Hence, the larger calculated sample number (*n* = 248) is chosen as a further basis for calculation to be able to achieve sufficiently good power for the secondary endpoints as well.

To ensure that the calculated minimum power will be achieved, there is a need to take possible drop-outs into account. Therefore at least 10% more subjects will be necessary, which results in a total of 273 participants. In consideration of the balanced design, the final target equals in a rounded up total number of 280 patients.

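### A normality pre-test picks the pain analysis, although pain sets the trial size, is rated nine times in hospital after surgery, and has no fixed summary and no stated use of the pre-operative rating

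*Protocol article*

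**What the plan says.** Under Statistical methods for primary and secondary outcomes {20a}, the protocol article states: "To ensure normal distribution, the Kolmogorov–Smirnov test will be conducted prior to further analyses". Variables judged parametric then go to Student's t-test and the others to Mann–Whitney. The same section adds a multivariable linear regression for continuous outcomes, with postoperative NRS as an example. The covariates it names are analgesic and sedative use during and after surgery. Other confounders are to be chosen in advance but are not listed. Sensitivity analyses with and without adjustment are promised.

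The pain hypothesis (Objectives {7}) reads: "NRS values are lower in the intervention group than in the control". It gives no time point.

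Pain is rated before surgery, when patients are visited and "they will be asked to rate their current level of pain using the NRS". In the recovery room, "After extubating objective data will be collected in the recovery room every 15 min for a total duration of 1 h". On the ward it is rated on days 1 to 5. Table 1 marks V1, V3a–V3d, V4–V8 and the three-month visit V9.

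Sample size {14} explains that "the effect on pain severity is also of great interest as a (secondary) endpoint" and takes the pain figure as the basis for recruitment: "For effects on pain intensity, an effect size of 0.325 can be calculated", and "When power is set at 0.8 and significance level at 5%, the resulting sample size amounts to a total of 248 subjects". The delirium calculation alone gave 220.

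**The concern.** Three things do not fit together.

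- **The pre-test.** It cannot deliver normality; it can only fail to reject it. Used as a switch, it makes the reported contrast (a mean difference or a rank comparison) depend on the observed data. On an integer 0–10 scale it will often reject for discreteness alone, and the outcome can differ between visits.
- **The outcome value.** Both named tests need one value per patient, but there are nine in-hospital postoperative ratings and nothing says which rating, or which summary of them, is compared.
- **The pre-operative rating.** Pain before hip or knee surgery is likely to predict pain afterwards. The V1 rating is scheduled, but no use of it is stated.

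Pain is secondary, but it is the reason for moving from 220 to 248 before dropout. An endpoint that carries that weight should have one defined result.

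**Working it through.** **Inputs from the protocol article.** Sample size {14}: d = 0.325, power 0.8, alpha 5%, total 248 (124 per arm at 1:1); for opioid use d = 0.36, at least 101 per group. Sidedness is not stated. Ratings: 4 in the recovery room + 5 on the ward = 9.

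**Assumed, not in the documents.** All correlations between ratings; the NRS mean and SD used in simulation.

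**1. Reproducing 248.** Noncentral-t power with noncentrality d·√(n/2). For Mann–Whitney, n is multiplied by the asymptotic relative efficiency 3/π (normal parent).

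| Test | Total N for d = 0.325 |
|---|---|
| One-sided t | 236 |
| **One-sided Mann–Whitney** | **248** |
| Two-sided t | 300 |
| Two-sided Mann–Whitney | 314 |

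For one-sided Mann–Whitney at n = 124: effective n = 124 × 3/π = 118.4, noncentrality = 0.325 × √59.2 = 2.50, power 0.802. At n = 123 power is 0.799, so 124 per arm is the minimum. The same variant gives 101 per group for d = 0.36, matching the opioid figure. The sizing therefore corresponds to one fixed test on one value per patient.

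**2. How often the pre-test rejects.** Normal scores rounded to integers 0–10, mean 3.5, SD 2, n = 124, Kolmogorov–Smirnov with estimated mean and SD: 64% of samples rejected. Over means of 2 to 5 and SDs of 2 to 2.2, rejection ran from 46% to 99%. With an approximate Lilliefors cut-off it was essentially 100%. The switch thus depends on chance and on the software variant.

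**3. Does that damage error rates?** Same scenario, 124 per arm, 6,000 runs, two-sided 5%, with Mann–Whitney used if either arm rejects. Type I error was about 0.05 for the two-stage rule and for each test alone. Power at d = 0.325 was about 0.68 for the two-stage rule, 0.70 for t and 0.68 for Mann–Whitney. The two tests disagreed on significance in about 2% of null runs and 5% of runs with an effect. Skewed data were not examined.

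**4. If all nine ratings were tested separately at 0.05.** Independent: 1 − 0.95⁹ = 0.37. Equally correlated, two-sided, by simulation: 0.33, 0.27 and 0.20 at correlation 0.3, 0.5 and 0.7.

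**5. What the pre-operative rating could add.** Adjustment raises the effective effect to d/√(1 − r²). Two-sided t at 124 per arm:

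- single rating, unadjusted: noncentrality 0.325 × √62 = 2.56, power 0.72
- r = 0.3: 0.325/√0.91 = 0.341, power 0.76
- r = 0.5: 0.325/√0.75 = 0.375, power 0.84

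One-sided, the unadjusted figure is 0.82, so the gap between 0.72 and 0.80 reflects sidedness and is not caused by the pre-test.

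**The case against.** The best defence has four parts.

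- **The article is condensed.** The choice of pain summary and the covariate list are commonly left to an analysis plan, which is not shown. This limits what can be said about the V1 rating. A reader might infer that it is never used; the documents support only that no use is stated, since the confounders are not listed. It does not excuse the pre-test, which is a rule written into this text.
- **A linear regression of NRS is also planned.** True, but it inherits the undefined pain value. Its named covariates are intra- and postoperative medication, measured after randomisation, and pain medication is itself a hypothesised outcome. Adjusting for it can remove part of the intervention's effect.
- **Nobody says that nine tests will be run.** Correct. A reader might infer nine separate tests at 0.05 and a 20–33% false-positive risk. That risk is conditional on such an analysis, which the text neither states nor rules out.
- **The pre-test is nearly harmless numerically.** In the rounded-normal scenario this stands. A reader might infer from the 64% rejection rate that inference is badly distorted; step 3 shows otherwise. What remains is that the effect measure is not fixed in advance.

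A larger gain can also be claimed. Averaging all nine ratings would give two-sided power of 0.93 or 0.85 at correlation 0.5 or 0.7. That assumes the same effect in the recovery room and on day 5, and equal correlation throughout. The documents support neither, so the conclusion does not rest on it.

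**Conclusion.** The point holds as a moderate weakness in a secondary endpoint that nevertheless sizes the trial; the primary delirium comparison is not affected. The analysis section leaves the test to the data and the pain value undefined, while the sizing matches one particular test on one value. The cost is a result that is not unique, room to choose among ratings after the fact, and unclaimed precision: two-sided power of 0.72 against 0.76–0.84 if the V1 rating correlates 0.3–0.5 with the postoperative value. Those correlations are assumed. The arithmetic also shows that 248 rests on an unstated one-sided test, which is a separate matter.

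**What to change.** Delete the Kolmogorov–Smirnov step. Before unblinding, pre-specify one postoperative pain endpoint at a single time point or over a single window: for example, separate recovery-room and ward means with one designated as main. Analyse it by ANCOVA or a linear mixed model with arm, V1 NRS, gender (the randomisation stratum) and centre. A mixed model that uses all available ratings keeps patients discharged before day 5; a simple patient mean would average different windows for them. Show other time points descriptively. For opioid dose and NOL, name one test in advance.

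The cost is wording only, since every rating needed is already scheduled. The downside is small: a single summary averages over phases of recovery, and the weight given to recovery-room and ward ratings has to be chosen deliberately. An equal-weight mean of all nine would give four-ninths of the weight to one hour.
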